##### DATA EVALUATION: CRITERIA FOR EVALUATION OF OBJECTIVES

All endpoints will be compared between the experimental vaccine group (+CPG 7909) and the control vaccine group (+placebo).

A substudy will compare endpoints in the two (non-randomised) treatment groups (on HAART vs. no HAART)

**PRIMARY ENDPOINTS:**

*At six months after 2nd vaccination with Prevenar.*

- Pneumococcal vaccine high responders defined as 2-fold increase and IgG levels ≥1 µg/mL to at least 5 of 7 pneumococcal serotypes (by quantitative IgG measurements)

**SECONDARY ENDPOINTS:**

**IMMUNOGENICITY**

*At three months after 1st vaccination with Prevenar.*

- Pneumococcal vaccine high responders defined as 2-fold increase and IgG levels ≥1 µg/mL to at least 5 of 7 pneumococcal serotypes (by quantitative IgG measurements)
- Opsonophagocytic activity for serotypes 6B, 14, 19F and 23F expressed as titers
- Serotype-specific antibody response defined as 2-fold increase and IgG levels ≥1 µg/mL
- Serotype-specific antibody response defined as change in IgG levels

*At six months after 2nd vaccination with Prevenar.*

- Opsonophagocytic activity for serotypes 6B, 14, 19F and 23F expressed as titers
- Serotype-specific antibody response defined as 2-fold increase and IgG levels ≥1 µg/mL
- Serotype-specific antibody response defined as change in IgG levels
- Cellular immune response

*At one month after vaccination with Pneumo Novum.*

- Pneumococcal vaccine high responders defined as 2-fold increase and IgG levels ≥1 µg/mL to at least 5 of 7 pneumococcal serotypes (by quantitative IgG measurements)
- Opsonophagocytic activity for serotypes 6B, 14, 19F and 23F expressed as titers
- Serotype-specific antibody response defined as 2-fold increase and IgG levels ≥1 µg/mL
- Serotype-specific antibody response defined as change in IgG levels
- Geometric Mean Antibody Concentrations With the Standard Enzyme Immunoassay for serotypes 1, 4, 7F, 9V, 14, 18C and 19F

**PHARYNGEAL COLONIZATION**

*At six months after 2nd vaccination with Prevenar.*

- Number of individuals with pneumococcal colonization

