A recent dose-ranging trial with conjugate pneumococcal vaccine in seniors (70+) found that a double dose of Prevenar (1.0 ml) was significantly more immunogenic than a single dose (0.5 ml). A dosing of 2.0 ml (four doses of Prevenar) was not more immunogenic than a dosing of 1.0 ml. Increasing the dose of Prevenar was not associated with more injection site reactions and no severe reactions were observed. 84% of the participants reported only mild pain after vaccination{{130 Jackson,L.A. 2007;131 Jackson,L.A. 2005; }}.

The primary disadvantage of the current Prevenar vaccine is that it covers only 7 pneumococcal serotypes and therefore approximately 45% of the pneumococcal infections in adults in Denmark in contrast to Pneumo Novum; which covers approximately 70% {{141 Nielsen,S.V. 1996; 80 Lockhart,S.P. 2006; }}. However a booster effect in HIV-patients has been seen when a conjugated vaccine is administered and followed by the polysaccharide vaccine. This was first observed by Kroon et al{{36 Kroon,F.P. 2000; }} and long term immunity from a conjugated vaccine booster approach was presented by a French group at the 14th Conference on Retroviruses and Opportunistic Infections (CROI) in February 2007{{85 Lévy, Y. 2007; }}. Their primary endpoint was the proportion of vaccine highresponders (defined as 2-fold increase and IgG levels ≥1 µg/mL to at least 5 of 7 pneumococcal serotypes) in the two groups. Although not statistical significant there were more high responders (13% versus 4%, p=0.08) in the prime-boost group versus the polysaccharide vaccine alone group at week 96. The advantage of using a conjugate+polysaccharide pneumococcal vaccination regimen is that the conjugate vaccine primes the immune system resulting in a more immunogenic response to the following polysaccharide vaccine than if the polysaccharide vaccine is given alone. However, 13% high responders after 96 weeks using an optimized pneumococcal vaccination strategy for HIV infected adults is not optimal and there is a need for a better pneumococcal vaccine regimen.

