**Secondary Objectives:**

- To compare the qualititative (functional) antibody response to pneumococcal vaccination with or without CPG 7909
- To evaluate safety and tolerance of CPG 7909 as a pneumococcal vaccine adjuvant
- To analyze changes in pneumococcal carrier status after pneumococcal vaccination
- To analyze the predictive value of immune activation/status markers such as CD4 count and sCD163 (at the time of vaccination) for the immune response after pneumococcal vaccination.
- To compare antibody responses to pneumococcal vaccination in patients receiving HAART and patients not receiving HAART
- To analyze cellular activity and response before and after vaccination

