##### PNEUMOCOCCAL CARRIAGE

Pneumococcal vaccination can affect pharyngeal carriage of pneumococci. Pneumococcal pharyngeal colonization may also affect the immune response to pneumococcal vaccination{{86 Frazao,N. 2005; }}. Therefore it is important to establish carrier status before and after pneumococcal vaccination. Oropharyngeal colonization will be tested in the posterior pharynx using a BBL culture swap (Becton Dickson Microbiology Systems, Cockeysville, MD, USA) thru the oral cavity. Samples will be labeled with the individuals study ID number, frozen at -20°C within few hours and later shipped to Statens Serum Institut, where isolation, culturing and serotyping will take place. This will take place at day 0 and again during follow-up at day 270.

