# SCHEDULE OF ASSESSMENTS/PROCEDURES

| **Assessments/ Procedures** | **Baseline** | **Vaccination** | | | **Follow-up** | | | |
| --- | --- | --- | --- | --- | --- | --- | --- | --- |
| **Study Day** | **Predose** | **Day 0 (1)** | **Day 90 ± 14 (2)** | **Day 270 ± 30 (2)** | **Day 90 ± 14 (3)** | **Day 270 ± 30 (4)** | **Day 300 ± 30 (4)** | |
| Written Informed Consent | X |  |  |  |  |  |  | |
| Inclusion/Exclusion Criteria | **X** |  |  |  |  |  |  | |
| Medical History and Demographics | **X** |  |  |  |  |  |  | |
| Pregnancy Test**(5)** | **X** |  | **X** | **X** |  |  |  | |
| Randomization | **X** |  |  |  |  |  |  | |
| Conjugate pneumococcal vaccine ± CPG 7909 **(6)** |  | **X** | **X** |  |  |  |  | |
| Polysaccharide pneumococcal vaccine ± CPG 7909 **(6)** |  |  |  | **X** |  |  |  |  |
| **Safety** |  |  |  |  |  |  |  | |
| Physical Examination |  | **X(7)** | **X(7)** | **X(7)** | **X(8)** | **X(8)** | **X(8)** | |
| Bloodpressure and Heartrate |  | **X(7)** | **X(7)** | **X(7)** | **X** | **X** | **X** | |
| Lab Safety Tests**(9, 10)** | **X** |  |  |  | **X** | **X** | **X** | |
| HIV Control Parameters**(11)** | **X** |  |  |  | **X** | **X** | **X** | |
| Adverse Events**(12)** |  | **X** | **X** | **X** | **X** | **X** | **X** | |
| **Efficacy** |  |  |  |  |  |  |  | |
| Functional antibody response | **X** |  |  |  | **X** | X | X | |
| Quantitative antibody response | **X** |  |  |  | **X** | **X** | **X** | |
| Oropharyngeal swap | **X** |  |  |  |  | **X** | **X** | |
| Immunologic markers **(13)** | **X** |  |  |  | **X** | **X** | **X** | |

1. Day 0 vaccination is conducted after all baseline assessments/procedures are made.
2. Day 90 follow-up and vaccination can vary by 14 days
3. Follow-up is done before proceeding to 2nd vaccination
4. Follow-up day 270 and day 300 is allowed to vary by 30 days.
5. Women of childbearing potential only.
6. According to randomization.
7. Participants asked to stay in for at least ½ hour post-vaccination. A physical examination incl. BP and HR will be made before discharge.
8. Physical examination will be made on participants request or if the investigator finds it relevant.
9. Complete bloodcount, serum chemistry and liver parameters
10. If a participant withdraws prematurely, lab safety tests must be done within approximately one week of participant withdrawal
11. Viral load (HIV RNA) and CD4-count

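### The day 270 carriage endpoint counts any pneumococcus although isolates are serotyped, so an effect confined to the seven Prevenar types is diluted

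*Protocol*

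**What the plan says.** Under PHARYNGEAL COLONIZATION the protocol gives one secondary endpoint, timed "At six months after 2nd vaccination with Prevenar": "Number of individuals with pneumococcal colonization". No serotype qualifies it. The matching secondary objective is equally general: "To analyze changes in pneumococcal carrier status after pneumococcal vaccination".

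The PNEUMOCOCCAL CARRIAGE section explains why swabs are taken ("Pneumococcal vaccination can affect pharyngeal carriage of pneumococci") and sends them to a reference laboratory "where isolation, culturing and serotyping will take place". It names two swab days, 0 and 270.

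PROCEDURES places Prevenar at days 0 and 90 and Pneumo Novum at day 270, with CPG 7909 or placebo added each time. The carriage endpoint is timed from the second Prevenar dose, so I read the day 270 swab as preceding any effect of the polysaccharide vaccine. BACKGROUND says of Prevenar that "it covers only 7 pneumococcal serotypes and therefore approximately 45% of the pneumococcal infections in adults in Denmark".

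In the SCHEDULE OF ASSESSMENTS/PROCEDURES, the row "Oropharyngeal swap" is marked at baseline, day 270 and day 300. No endpoint uses a day 300 swab.

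**The concern.** At day 270 the only vaccine on board is directed at seven serotypes. The main antibody endpoints at the same visit are matched to it: the high-responder definition uses those seven types, and opsonophagocytic activity is read for four named types. Carriage is the exception. It pools covered and uncovered strains in one count, although the laboratory will already have told them apart.

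A null result on the pooled count would then have two readings: no effect on carriage, or fewer vaccine-type carriers offset by carriers of other types. An effect limited to vaccine types would also look smaller than it is.

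**Working it through.** **The plan's own figure.** The protocol sizes the trial on the high-responder endpoint only. The usual two-proportion formula (pooled variance under the null, two-sided 5%, 80% power, no continuity correction) with 30% against 60% gives 42 per group. Allowing for 10% drop-out, 42 / 0.9 = 46.7, so 47 per group and 94 in total. Both figures match the protocol, and the same formula is used below. The protocol states no carriage rate, carriage effect or power for carriage.

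**Dilution.** Treat each carrier as carrying one strain, and let

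- s = share of control-arm carriers whose strain is a Prevenar type;
- r = relative reduction in vaccine-type carriage from adding CPG 7909;
- f = fraction of those lost carriers who carry another type instead.

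Both arms receive Prevenar, so r is the added effect of the adjuvant. If total control-arm carriage is T, the CPG 7909 arm has T − T·s·r·(1 − f). The any-type ratio is therefore 1 − s·r·(1 − f), whatever T is. The vaccine-type ratio is 1 − r.

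All three inputs are assumptions. The protocol's 45% is a share of infections, not of carriage, so it serves only as the middle of a range. With r = 50% the vaccine-type ratio is 0.50, and the any-type ratio is:

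| s | f = 0 | f = 0.5 | f = 1 |
|---|---|---|---|
| 20% | 0.90 | 0.95 | 1.00 |
| 45% | 0.775 | 0.8875 | 1.00 |
| 70% | 0.65 | 0.825 | 1.00 |

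For example, s = 45% and f = 0 give 1 − 0.45 × 0.50 = 0.775.

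**Fewer events against a larger contrast.** Take T = 20% and s = 45%, again assumed. Vaccine-type carriage is 0.20 × 0.45 = 9.0% against 4.5%. Any-type carriage is 20.0% against 20.0 − 4.5 = 15.5% with f = 0, or 17.75% with f = 0.5. The numbers needed per arm for 80% power are:

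- vaccine-type: 487;
- any-type, f = 0: 1131;
- any-type, f = 0.5: 4747.

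In this example the restricted count is more sensitive although it has fewer events.

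**What the trial can actually see.** With 42 per arm the example expects 42 × 0.09 = 3.8 against 42 × 0.045 = 1.9 vaccine-type carriers. Over T = 5% to 40% and s = 20% to 70%, with r = 50% and f = 0, power is about 5% to 35% for vaccine-type carriage and about 3% to 27% for any-type carriage (normal approximation, counting rejections in the direction of the effect).

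**The case against.** The any-type count agrees with the stated objective, which concerns carrier status in general, and net carriage is a legitimate quantity. The carriage section also gives a second reason for swabbing, that colonisation may influence the vaccine response, and does not limit it to vaccine types. This stands: the endpoint as written is neither wrong nor contradictory.

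A reader might infer that a difference driven by uncovered strains would be wrongly credited to the regimen. The documents do not support that. The comparison is between randomised arms that both receive Prevenar, so a difference beyond chance is an effect of adding CPG 7909, whichever strains carry it. Nor do they say that an innate immune stimulant can act on carriage of seven types only.

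It may also be said that a serotype breakdown is detail for the statistical analysis plan, which is not at hand. Nothing in the protocol prevents one. But the protocol itself fixes what is counted, and that is the place to say that the serotypes will be used.

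Finally, the trial is too small for carriage under either definition. That also stands, and it limits what the change can achieve.

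**Conclusion.** The point holds as a minor improvement to an unpowered secondary endpoint. Dilution follows from the definition for any vaccine-type share below 100%, provided the adjuvant's effect on carriage runs through the seven types. Its size is unknown. Under an assumed halving of vaccine-type carriage, the any-type reduction is 10% to 35% for shares of 20% to 70% without replacement, and it tends to zero as replacement becomes complete.

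Two stronger readings should be resisted. One is that the dilution is known to be the 0.775 case: that value borrows a share of infections for a share of carriage. The other is that replacement will cancel the effect: it is a logical possibility that the documents never mention. Splitting the count makes the result easier to interpret, but does not make 94 participants enough for a confirmatory carriage comparison.

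The disagreement between the carriage section and the schedule over a day 300 swab is a real inconsistency, but a separate one. It lends no weight to the dilution argument.

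**What to change.** Under PHARYNGEAL COLONIZATION, compare the arms at day 270 on two counts: individuals carrying a Prevenar serotype, and individuals carrying any other serotype. Name the seven types in the definition and say how a person carrying both kinds is counted. Keep any-type carriage as the net measure and label all three exploratory.

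The cost is wording only, because serotyping is already planned. The downside is fewer events in each category and so wide intervals.

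Separately, reconcile the PNEUMOCOCCAL CARRIAGE section with the schedule on whether a day 300 swab is taken. If it is kept, state its purpose. By then participants have also received the 23-valent vaccine, so the two-way split no longer fits. Classify those isolates as Prevenar types, additional types covered by Pneumo Novum, and types covered by neither.

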**PREDICTORS OF ANTIBODY RESPONSE**

*At baseline.*

- Predictors for vaccine response at six months after 2nd vaccination with Prevenar,

**SECONDARY ENDPOINTS:**

**REACTOGENICITY AND SAFETY IN ALL SUBJECTS**

**ANALYSIS POPULATIONS:**

**Safety population:** all patients who received at least one vaccination.

- Occurrence of solicited and general symptoms during the 4-day (day 0 to Day 3) period after each vaccination dose
- Occurrence of unsolicited symptoms up to 1 month after each vaccination
- Changes in CD4-count and viral load during the study

Safety will be assessed by physical examination, adverse events (according to common toxicity criteria version 2.0), laboratory tests, and HIV control parameters (HIV RNA and CD4-count).

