##### MAIN ASSESSMENT PARAMETERS:

Efficacy: *Primary*

- Quantitative measurement of specific anticapsular antibodies (7 serotypes)

*Secondary*

- Functional activity of specific anticapsular antibodies (pneumococcal serotypes 6B, 14, 19F and 23F)
- Microbiological changes in pneumococcal pharangyal colonization
- Baseline CD4-count and measurement of sCD163
- Measurements of cellular response, i.e. IFN-γ

Safety/Tolerability:

- Adverse events (AEs).
- Serious adverse events (SAEs)
- Number and intensity of adverse and serious adverse events
- Laboratory tests (hematology, clinical chemistry i.e. viral load (HIV RNA) and CD4-count).
- Physical examination.

**STUDY DESIGN:** Placebo-controlled, randomized, double-blinded study.

**PLANNED TOTAL SAMPLE SIZE:** 94 participants (47 per group).

**CENTER & RECRUITMENT:** The study will be conducted in the Department of Infectious Diseases at Skejby Hospital, Aarhus University Hospital. HIV patients receiving care at other hospitals may also be invited to participate in the study at Skejby Hospital. HIV-infected individuals will be recruited by invitation and patient information sent by regular mail to their home addresses; unless they have previously asked not to receive letters from the department. Study information will also be available in relation to their regular, scheduled consultation at the hospital’s HIV clinic. Individuals interested in study participation may contact the primary investigator or study nurse by phone. A booking for the first visit in relation the study will be made during this conversation and the participant can ask questions regarding the study. After completion of the first study the participant will book a time for his/hers 2nd visit and so fort. A thorough written and oral patient study information will be given before consent is obtained. If the individuals wish to have more time to consider his/hers study participation or if they prefer to have a friend or relative at their side to assist them in their decision they may postpone their decision. Consenting patients that pass the inclusion/exclusion criteria will be enrolled in the study.

400 HIV infected individuals have regular control visits at the Department of Infectious Diseases, Skejby Hospital. Enrolment will be terminated when 94 subjects have been enrolled.

**TEST DRUGS AND FORMULATIONS:** CPG 7909 (a synthetic Toll-like receptor 9-agonist) formulated in PBS buffer.

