**Secondary endpoints**

Comparison of endpoints between the study groups will be done by Poisson regression (dichotomous endpoints) or linear regression (continuous endpoints), adjusted for appropriate potential confounders.

Predictors for achieving a high vaccination response (classified as a high responder) at six months after 2nd vaccination with Prevenar will be estimated by multivariate Poisson regression.

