##### ETHICAL CONSIDERATIONS

Applications to the Danish Data Protection Agency, Regional Ethical committee and Danish Medicines Agency will be submitted. The 23-valent polysaccharide pneumococcal vaccine (i.e. Pneumo Novum) has been on the market since early 1980’s and has been very well tolerated in both immunocompetent and immunocompromised individuals. Only some minor adverse effects (local swelling, nausea, local erythema) and very few serious adverse have been reported even in severely immune compromised patients. The 7-valent conjugated pneumococcal vaccine (Prevenar) has been part of the American children vaccination program since 2000 and several Western European countries have since followed (in accordance with WHO recommendations). Post-marketing surveillance and vaccine trials (including trials on both HIV-positive children and adults) have shown that the vaccine is very well tolerated{{21 Madhi,S.A. 2005;20 Madhi,S.A. 2005; 80 Lockhart,S.P. 2006; 22 Klugman,K.P. 2003; 3 Kamchaisatian,W. 2006; 15 Feikin,D.R. 2001; }}. We therefore consider it unlikely that the vaccines will cause more than minor temporally discomfort. In the background section of this protocol and in the investigator’s brochure (APPENDIX 1) we have discussed the safety of TLR9-agonists. In general the safety of TLR9-agonists has been very good in all trials with TLR9-agonists. At low doses in vaccine trials (like the 1 mg planned in this study) there seems to be a slight increase in the frequency of injection site reactions relative to vaccine alone, but not increased severity as these are generally mild. The clinical experience to date indicates that CPG 7909 treatment (and TLR9-agonist treatment in general) of normal humans, cancer patients or individuals infected with HIV or Hepatitis C does not induce autoimmune disease, kidney disease, liver disease, spleen or bone marrow disease. In all the studies of TLR9-agonist the maximal tolerated dose in humans has never been reached. Therefore a dosing of 1 mg CPG 7909 with each pneumococcal vaccination appears safe and well below the upper limit used in other TLR9-agonist trials. The benefit for all study participants who receive all study vaccinations is that they receive the most effective pneumococcal vaccination known at present time. Our hypothesis is that TLR9-agonist adjuvanted pneumococcal vaccination will substantially improve the magnitude and duration of seroprotection in HIV-infected individuals; thereby reducing morbidity and mortality caused by pneumococcal disease. Thus, on a individual level participants reduce their risk of pneumococcal infection and on a larger scale they contribute to our knowledge of TLR9-enhanced pneumococcal vaccination. Not only HIV-patients; but also elderly, cancer patients and other immune compromised individuals could benefit from this vaccination approach in the future.

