12. Intensity of adverse events graded according to common toxicity criteria (CTC version 2.0).
13. Immunologic markers (i.e. sCD163) that may predict antibody response and cellular immune response.

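### The symptom endpoints record only whether a reaction occurred, and the visible protocol text specifies no between-arm comparison of the CTC grade it requires

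*Protocol*

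**What the plan says.** - **Endpoints.** Under SECONDARY ENDPOINTS: REACTOGENICITY AND SAFETY IN ALL SUBJECTS, the two symptom endpoints are "Occurrence of solicited and general symptoms during the 4-day (day 0 to Day 3) period after each vaccination dose" and "Occurrence of unsolicited symptoms up to 1 month after each vaccination". Neither mentions grade. The closing sentence of that section does say that safety is assessed by, among other things, "adverse events (according to common toxicity criteria version 2.0").
- **Parameters.** MAIN ASSESSMENT PARAMETERS lists "Number and intensity of adverse and serious adverse events" under Safety/Tolerability.
- **Grading.** ADVERSE EVENTS (AEs) and ASSESSMENT OF INTENSITY both require the CTC scale. Note 12 to the SCHEDULE OF ASSESSMENTS/PROCEDURES repeats it: "Intensity of adverse events graded according to common toxicity criteria (CTC version 2.0").
- **Comparison.** DATA EVALUATION says that all endpoints are compared between the CPG 7909 and placebo groups. Under STATISTICAL ANALYSES, Secondary endpoints: "Comparison of endpoints between the study groups will be done by Poisson regression (dichotomous endpoints) or linear regression (continuous endpoints"). No ordinal method is named.
- **Safety reporting.** Safety data are to be listed and summarised, with adverse events given as proportions with 95% confidence intervals in a model table. That table is not shown in the text available.
- **What is expected.** ETHICAL CONSIDERATIONS says that low-dose TLR9 agonists slightly raise the frequency of injection-site reactions, "but not increased severity as these are generally mild".

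**The concern.** Intensity is named as a parameter and graded, but it drops out where the endpoints are fixed. DATA EVALUATION attaches the between-arm comparison to endpoints, so a parameter that is not an endpoint has no comparison written for it.

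This matters because safety and tolerance of CPG 7909 is a secondary objective of a Phase I trial, and the protocol itself makes a statement about severity. A participant who would have had a mild reaction on placebo and has a moderate or severe one on CPG 7909 counts the same under occurrence. The trial could report similar reactogenicity in the two arms while moderate or severe reactions were clearly more frequent with the adjuvant.

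A second, weaker issue concerns injection-site pain only. BACKGROUND reports that "84% of the participants reported only mild pain after vaccination" in a dose-ranging trial of Prevenar in people aged 70 and over. If that means 84% had some pain, and if the rate carries over to this population, occurrence of pain has little room to rise.

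**Working it through.** **The plan's own figure.** ESTIMATED SAMPLE SIZE gives 42 per group for 30% vs 60% (two-sided 0.05, power 0.80):

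n = [1.96·√(2·0.45·0.55) + 0.8416·√(0.30·0.70 + 0.60·0.40)]² / 0.30² = (1.379 + 0.565)² / 0.09 ≈ 42

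With 10% drop-out, 42/0.90 = 46.7, so 47 per group and 94 in total. This reproduces. It concerns the primary endpoint; no power is stated for reactogenicity. The illustrations below use 47 per arm and two-sided 5%. All grade distributions are assumptions, written none/mild/moderate/severe.

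**1. Severity shift with occurrence unchanged.** Control is 16/68/14/2%, so any reaction is 84% and grade 2 or higher is 16%. With CPG 7909, any reaction stays at 84% and grade 2 or higher becomes 40%, so mild falls to 84 − 40 = 44%.

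- Occurrence: 84% vs 84%, so rejection is about 5%, the false-positive rate.
- Grade 2 or higher, pooled two-proportion test, p̄ = 0.28: SE₀ = √(2·0.28·0.72/47) = 0.0926 and SE₁ = √[(0.16·0.84 + 0.40·0.60)/47] = 0.0893. Power = Φ[(0.24 − 1.96·0.0926)/0.0893] = Φ(0.655) ≈ 74%. Simulation gives 75 to 76%.
- Maximum grade, Wilcoxon test: 46 to 48% by simulation.

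That occurrence misses such a shift follows from its definition and holds at any control rate.

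**2. Shift across all grades (proportional odds).** With an odds ratio of 3 from the same control, any reaction goes from odds 0.84/0.16 = 5.25 to 15.75, i.e. 94%. Grade 2 or higher goes from odds 0.16/0.84 = 0.190 to 0.571, i.e. 36%. Power from 20,000 simulated trials:

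| Control distribution (%) | Odds ratio | Occurrence | Maximum grade |
| --- | --- | --- | --- |
| 16/68/14/2 | 3 | 37% | 73% |
| 16/76/7.5/0.5 | 3 | 37% | 61% |
| 10/84/5/1 | 3 | 26% | 49% |
| 12/84/3.5/0.5 | 3 | 30% | 44% |
| 50/34/14/2 | 3 | 72% | 81% |
| 16/68/14/2 | 1.5 | 11% | 15% |

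The gain from using grade runs from 4 points to 36 points, depending on the assumptions.

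**3. Room to rise, injection-site pain only.** If 84% is the control rate of any pain, the prevalence ratio cannot exceed 1/0.84 = 1.19. Power against 95% in the CPG arm, with p̄ = 0.895: SE₀ = √(2·0.895·0.105/47) = 0.0632 and SE₁ = √[(0.84·0.16 + 0.95·0.05)/47] = 0.0622. Then Φ[(0.11 − 1.96·0.0632)/0.0622] = Φ(−0.22) ≈ 41%. A power of 80% needs about 99.6% in the CPG arm. From lower control rates, the rate detectable with 80% power is 58% (from 30%), 77% (from 50%) and 92% (from 70%), so the constraint disappears for less common symptoms.

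**The case against.** The strongest reply is that the deciding content may simply not be visible. The model table under Safety data is missing from the text, and if it splits events by grade, proportions with confidence intervals by grade and arm would already supply much of what is asked. The reactogenicity section itself refers to CTC, which is a grading scale. Safety has its own descriptive heading, no safety test or power is claimed, and an analysis plan that is not shown could add detail. This stands to the following extent: a reader might infer that severity will not be compared at all, and the documents do not support that. They support only that no severity endpoint and no between-arm severity comparison appear in the visible text, while the endpoints the protocol does fix leave out a parameter it names.

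A reader might also infer that the yes/no comparison sits near its ceiling for symptoms generally. That is not supported either. The 84% concerns pain after Prevenar in people aged 70 and over. Its wording can also mean nothing worse than mild, with pain-free people included, which implies no ceiling. It says nothing about general or unsolicited symptoms, and the third dose is Pneumo Novum.

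Finally, an odds ratio of 3 is generous when the protocol expects only a slight rise in reaction frequency. At 1.5 neither measure has useful power. The power figures are therefore illustrations and not a forecast.

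**Conclusion.** The point holds as a mismatch inside the protocol. Intensity is a named parameter and is graded, but the symptom endpoints put up for comparison are occurrence only. A worsening from mild to moderate or severe cannot show in them, whatever the control rate. In the illustration, a 24-point rise in grade 2 or higher reactions is detected about 5% of the time by occurrence and about 75% of the time by the grade 2 or higher proportion. When the effect raises occurrence as well, the gain ranges from small to large with the assumed distribution and odds ratio. Limited room for occurrence to rise is a possibility for injection-site pain only, conditional on how the 84% is read and on its carrying over to HIV-infected adults. The primary analysis and the sample size are untouched. This is a cheap improvement.

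**What to change.** In the reactogenicity endpoints, keep occurrence and add, for each solicited local and general symptom:

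- the maximum CTC grade (0 to 4) per participant after each dose, with the between-arm estimate and 95% confidence interval from a proportional-odds model adjusted for HAART status;
- the proportion of participants with grade 2 or higher, by arm, with 95% confidence intervals.

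Show the adverse-event table under Safety data by grade, if it does not already do so. State that these are estimates and not confirmatory tests. Any power gain should be quoted as a range with its assumptions.

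The cost is a few lines of text and more comparisons per symptom. No new visits or participants are needed, because grading is already required. One thing to confirm: the participant diary (Appendix 4) is not shown, and the list of case report form data names the start and duration of adverse events but not intensity, so both should be checked for a grade field. The new endpoint would also inherit the solicited window, which is days 1 to 4 under SOLICITED ADVERSE EVENTS and days 0 to 3 in the endpoint list; these two should be reconciled at the same time.
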